## Abstract

**Background:**

In 2019, global sleep surveys reported that 80% of adults want to improve their sleep quality, and in 2021, 45% were reported to be dissatisfied with their sleep. In 2025, among American adults, 37% reported sleep dissatisfaction and 38% reported not feeling energized after sleep. These findings are consistent with data from the 2016 nationally representative survey of Mexican adults (aged ≥18 years), in which 37% reported sleep problems.

**Objective:**

This protocol describes a pilot randomized controlled trial (RCT) testing whether a single personalized sleep intervention driven by machine learning (ML) using consumer wearable data can improve sleep scores compared with generic sleep hygiene education in healthy middle-aged adults from Mexico City.

**Methods:**

This pilot RCT plans to enroll 32 participants (16 per arm; stratified by sex) in Mexico City. All participants wear Samsung Galaxy Watch 4 devices for 60 days. During days 1‐30 (baseline), objective sleep data (10 variables related to duration, efficiency, sleep stages, movements, cycles, and recovery metrics) are collected. The control group receives generic sleep hygiene education. The experimental group receives personalized recommendations on day 30 based on the top predictive sleep parameters identified by ML models using Shapley Additive Explanations analysis and recursive feature elimination. The primary outcome is the sleep score (scale 1‐100; composite device metric) during days 31‐60, which is analyzed using analysis of covariance, with the baseline sleep score as a single covariate. The secondary outcome is the Pittsburgh Sleep Quality Index (PSQI) global score (scale 0‐21; subjective validation), which is assessed at baseline, day 30, and day 60.

**Results:**

The study is currently in progress. Recruitment started in August 2024 and ended in July 2025. Data collection is expected to be completed by December 2025. The study will compare 960 nights from the control group with 960 nights from the experimental group to explore whether ML interventions can improve sleep scores using wearable technology, generate a dataset from objective data for iterative model training and analysis, correlate objective and subjective sleep quality metrics, and establish whether a feasible framework for proactive sleep quality approaches can be developed. The results will be available by March 2026, and the findings will be submitted for publication within 6 months of study completion.

**Conclusions:**

This pilot study establishes the feasibility and preliminary effect size for ML-personalized sleep interventions using consumer wearables within a manufacturer-independent personalization framework. The approach combines objective device monitoring with a subjective measure (PSQI) to test whether precision targeting of individual sleep parameters outperforms generic recommendations. If validated, this methodology could advance sleep interventions from universal protocols toward individualized behavioral targeting. The resulting dataset will enable model refinement and provide preliminary evidence for scaling personalized sleep health interventions in healthy populations.

## Introduction

### Overview

Sleep is essential for health and productivity. Global sleep dissatisfaction has been reported by 35%‐45% of adults, and this is consistent with 37% of Mexican adults reporting sleep problems [1-5]. Sleep benefits are well researched, and they include (1) a healthy body through immune system efficiency [6,7], (2) healthy emotions through psychological well-being [8], and (3) a healthy mind through memory consolidation [9-11]. The negative consequences of poor sleep are also well researched, and they include heart disease [12], metabolic syndrome [13], high blood pressure [14], diabetes [15], obesity [16], common cold [6], higher probability of injury [17], and higher mortality risk [18-20].

### Demographic and Geographic Context

This pilot study will be conducted in Mexico City, a metropolitan area with over 21 million residents [21]. Adults aged 30‐60 years represent over 40% of Mexico’s economically active population [22], making this demographic relevant for sleep health research. Urban workers in Mexico City face unique sleep challenges, including long commutes, shift work, and environmental stressors, that may impact sleep quality [5,23,24]. National surveys indicate that 35%‐40% of Mexican adults sleep fewer than 7 hours per night, with 37% reporting sleep problems [4,5]. Mexico City’s context provides a useful setting to explore sleep intervention feasibility in a rapidly urbanizing environment [25,26].

### Knowledge Gap

Despite growing interest in wearable sleep technology, a significant knowledge gap exists regarding whether machine learning (ML) analysis of individual sleep patterns from commercial devices can generate actionable recommendations that improve objective sleep outcomes. No previous studies have examined whether sleep scores from wearables (Samsung Galaxy Watch [27] or equivalent) can serve as primary outcome measures for personalized ML-derived interventions validated against the Pittsburgh Sleep Quality Index (PSQI) [28]. Existing consumer sleep coaching, such as Samsung’s Sleep Coach, categorizes users into predefined “sleep animal” types based on general sleep patterns (sleep time, sleep consistency, and awake time) and provides standardized multiweek programs [29,30] without subjective validation. Recent advances focus on validation studies comparing device accuracy to polysomnography (PSG) and developing ML algorithms for sleep stage classification [31-34]. Samsung has collected over 716 million nights of sleep data (collected between June 2021 and May 2023 via the Galaxy Watch series) globally [35], and research using Samsung Galaxy Watch sleep scores as intervention targets remains unexplored.

### Study Uniqueness

This pilot study addresses the gaps in the literature by exploring if wearable sleep scores [27,29,30,36-43] can serve as primary outcome measures for personalized ML-derived interventions and showing if ML analysis of individual patterns can identify the predictors of improvement, with validation against the PSQI (structured 30-day correlation framework) [28], in healthy middle-aged Mexican adults, a population facing unique urban sleep challenges but underrepresented in sleep technology research. This represents a personalized, ML-driven sleep intervention using a consumer wearable sleep data source (sleep metrics) for personalization as well as primary outcome measures (sleep scores) and user subjective assessments, establishing a novel paradigm for sleep health.

### Core Methodological Innovation

This pilot study tests a single, focused innovation: a personalization framework that generates behavioral sleep interventions from ML analysis of individual patterns in consumer wearable data. Our innovation is the *methodology*, not the device, theories, or algorithms. We are not validating device accuracy or comparing algorithms. Existing studies have established these foundations [36-43]. We are testing whether personalized behavioral interventions derived from individual ML analysis of the sleep metrics of a consumer device can improve objective sleep scores better than generic sleep hygiene education. This methodology is intentionally device-agnostic. The same personalization framework can be applied to other manufacturers’ wearables, providing continuous numeric sleep data and sleep score scales. We perform tests within Samsung’s ecosystem to isolate the intervention effect (personalized vs generic) without confounding by device differences. If successful, this will establish a transferable approach that other researchers can replicate across manufacturers, potentially driving the field toward less proprietary and more user-centered sleep optimization tools.

### Sleep Measurements

There are 2 ways to measure sleep. The first involves subjective measures of sleep that assess patient-reported satisfaction and functional impact (essential domains reflecting clinical relevance) and have evolved from sleep diaries [44] into validated survey instruments like the gold-standard PSQI [28] for sleep quality and sleep patterns, the Epworth Sleepiness Scale for daytime sleepiness [45], the Patient-Reported Outcomes Measurement Information System for sleep disturbances [46], and the Sleep Health Index for general sleep health [47]. The second involves objective measures of sleep that capture physiological parameters not consciously perceived (sleep parameters [measurable components] such as efficiency, latency, architecture, and fragmentation). Sensors collect objective measures of sleep by measuring physical inputs [31-34,48-51]. The most important biomarkers for sleep tracking are heart rate, breathing rate, blood oxygen flow, and body movements [51,52].

Sleep devices can be subdivided by grade into (1) medical-grade devices (also called clinical-grade devices), such as the gold-standard PSG [53,54]; and (2) commercial-grade devices (also called consumer-grade devices or consumer sleep technology [55]), such as off-the-shelf smartwatches [43]. They can also be subdivided by their body proximity into (1) devices in contact with the body (wearables) like watches, patches, rings, and bands [56]; (2) devices near the body (nearables) like bedside stands and devices in or under the mattress [57]; and (3) devices inside the body (implants) like subcutaneous electroencephalography devices [58,59]. Crivello et al [60] categorized sleep monitoring technologies by deployment as follows: laboratory-based (eg, PSG and specialized electroencephalography), ambulatory or portable (eg, wearables, on-bed sensors, actigraphy devices, and contactless devices), and consumer integration (eg, smartphone apps and smart home sensors).

In 2019, the wearable sleep tracker segment represented 44% of global smart sleep-tracking products [57]. The most common body locations of wearables are the head, chest, wrist, and finger. The wrist is the most popular location, representing more than 58% of the segment in 2024 [61].

PSG is the gold standard for objective sleep measures, but requires expensive equipment. Type 1 PSG requires technologist labor and lab settings, while type 2 PSG can be performed at home with or without a technologist [53,54,62-66]. The cost of long-term sleep monitoring with type 1 PSG or type 2 PSG is very high [66-68]. However, PSG is instrumental in setting a baseline to compare recent technological advances with wearable objective measurements for identifying an affordable and noninvasive option for continuous monitoring [36,62,69-71].

As the lines between consumer and clinical devices are blurring [55], there is an ongoing debate regarding the trustworthiness of available technologies. In 2018, the American Academy of Sleep Medicine stated that for consumer sleep technologies to provide a diagnosis or treatment, they first need Food and Drug Administration clearance and testing against current gold standards [72]. Studies have reported overall overestimated sleep with these devices compared with PSG due to lower sensitivity to detect wake epochs [73] and more discrepancies in sleep disorder populations [74-76].

Commercial-grade wearable devices should be validated with PSG to ensure reliability. A study in 2017 reported high agreement between a commercial wearable device and PSG in good sleepers but low agreement in patients with insomnia [75]. Another study in 2019 showed comparable results for the rapid eye movement (REM) sleep phase [63]. A study in 2020 concluded that wearables can accurately measure sleep and cardiorespiratory variables in healthy people [77], and a recent study reported the accuracy of a wearable device in sleep stage identification [65].

This study focuses on healthy adults without diagnosed sleep disorders [78-81], as this population represents 63%‐67% of adults [82,83]. In 2004, only 9%-11% of people were considered to have chronic insomnia by the World Health Organization Regional Office for Europe [84]. In 2022, a study reported that 10%-15% of people have chronic insomnia with daytime consequences [85], and another source reported that up to 22% of people meet the insomnia sleep disorder criteria [86]. These findings align with the overall percentage of adults not getting enough sleep (33.3%-36.8%) from 2013 to 2022 [82,83].

### Sleep Quantity

Sleep quantity refers to the amount of daily time spent sleeping (sleep duration), measured in hour units. The American Academy of Sleep Medicine, the Sleep Research Society, and the National Sleep Foundation agree that adults (aged 18‐60 years) need a minimum of 7 hours of sleep each night [87,88], and a sleep duration less than that implies a sleep deprivation condition (insufficient sleep) [18]. The following variables can be considered for assessment: (1) time in bed (TIB), period from lights off to lights on; (2) total sleep time (TST), actual time spent sleeping (sleep quantity) consistently shorter than TIB unless efficiency reaches 100%; and (3) sleep efficiency ([TST / TIB] × 100).

There are four main disadvantages of relying on this metric in isolation: (1) quantity increase does not guarantee a positive correlation with sleep quality (eg, during the 2021 pandemic period, Americans were sleeping more [quantity], but sleep quality declined) [89]; (2) TIB can be misunderstood as TST (these are only equal if 100% sleep efficiency is achieved) [90-92]; (3) sleeping beyond a limit can have negative consequences, such as stroke [93] and intracerebral hemorrhage [94] (the National Sleep Foundation has recommended a maximum sleep duration of 9 hours [88]); and (4) sleeping time cannot provide valuable data on sleep architecture, including time spent in each of the 4 sleep stages, number of sleep cycles, distribution of sleep stages, and transition speed between sleep phases [90-92].

### Sleep Quality: Definition and Measurement

Sleep quality or restorative sleep represents a multidimensional construct encompassing both objective parameters and subjective restoration. Nelson et al [95] identified 4 core attributes: sleep efficiency, latency, duration, and wake after sleep onset. Contemporary understanding extends beyond these continuity attributes to include architecture components (adequate deep sleep for physical recovery, sufficient REM sleep for cognitive restoration, and optimal 4‐6 sleep cycles) and minimal fragmentation [95-99]. An increase in quantity does not guarantee a positive correlation with sleep quality [89]. The 2014 and 2015 survey results by the National Sleep Foundation showed an 11-point delta in sleep duration compared with the sleep quality score and a final 69/100 score for sleep quality [47]. Despite China’s records showing that the general population has an average sleep duration of 7.31 hours [100] and Chinese university students reporting an average sleep duration of 7.08 hours [101], studies on the prevalence of poor sleep quality have been published [102].

### Sleep Quality in Healthy Populations

Rosipal et al [103] identified objective components for sleep quality indexing in normal sleep. Moreover, O'Donnell et al [104] found significant subjective-objective relationships in healthy older study participants. Even healthy individuals show consequences, including cognitive decrements, mood alterations, fatigue, and behavioral adaptations (increased caffeine use).

### Related Studies

In 2018, Guillodo et al [105] concluded that wearables for sleep monitoring are acceptable, and de Arriba-Pérez et al [71] concluded that the use of consumer-grade wearables as sleep indicators is a feasible option, although some require more rigor. In 2023, Lins et al [106] concluded that the photoplethysmography technology of the Samsung Galaxy Watch 4 was comparable to the oscillometric reference method for blood pressure determination. Moreover, Gaiduk et al [36] reported the feasibility of measuring several relevant sleep characteristics with Samsung Galaxy Watch 4 as a sensor-based approach in a real-life setting, if some level of inaccuracy is accepted. In 2024, Alshamari and Althobaiti [107] compared wearable sleep tracker–related improvements and concluded that a WHOOP device can both improve the perception of quality and provide accurate measures of sleep and cardiorespiratory variables.

## Methods

### Conformance to Reporting Standards

This protocol conforms to the SPIRIT (Standard Protocol Items: Recommendations for Interventional Trials) 2013 Statement. The SPIRIT 2025 checklist of items to address in a randomized trial protocol is presented in Checklist 1.

### Trial Design

This is a parallel-group randomized controlled pilot trial with a 1:1 allocation ratio. Participants are stratified by sex (male/female) and randomized to either (1) a control group receiving generic sleep hygiene education or (2) an experimental group receiving personalized ML-derived behavioral recommendations.

The observation period is 60 days, which aligns with PSQI requirements for 30-day data collection periods. PSQI assessments are performed at (1) baseline (prior to device use), (2) day 30 (first monitoring period), and (3) day 60 (postintervention period). This enables subjective-objective correlation while establishing a baseline (days 1‐30) to be used as a covariate for intervention analysis (days 31‐60). While 30 days may be minimal for entrenching behavior change, this pilot will establish feasibility and preliminary effect sizes for future extended trials.

### Patient and Public Involvement

No patient or public involvement has been planned in the design, conduct, or reporting of this pilot trial owing to resource constraints for this project. Future definitive trials will incorporate patient and public involvement in intervention design, outcome selection, and dissemination strategies.

### Study Setting

This pilot study is conducted in Mexico City, a metropolitan area with over 21 million residents. Participants sleep in their habitual home setting while wearing a Samsung Galaxy Watch 4 continuously. All study interactions (consent, PSQI administration, device distribution, intervention delivery, and equipment return) occur in Mexico City through in-person meetings with a researcher.

### Eligibility Criteria

#### Eligibility Criteria Operationalization

The operationalization of the eligibility criteria is as follows:

Sleep disorder screening: structured interview regarding diagnosed disorders, medications, and medical consultations; self-declaration (no PSG screening)Medical/psychiatric assessment: standardized questionnaires (no chart review)Nationality and age: birth certificate upon requestActive workforce: full-time employment (≥40 hours/week) verified through documentationLimitations: self-report with documentation appropriate for a community-based pilot

#### Inclusion Criteria

The inclusion criteria are as follows: (1) Mexican nationality, (2) age 30‐60 years (minimizes age-related sleep physiology variability), (3) male or female gender, (4) active workforce status during the study, (5) residence in Mexico City during the study, (6) willingness and ability to use the wearable device for 60 days (at least during sleep), and (7) consent for providing sensitive personal data for the experiment.

#### Exclusion Criteria

The exclusion criteria are as follows: (1) diagnosis of chronic sleep disorders (eg, insomnia) requiring specific treatment, (2) major psychiatric or neurological conditions affecting sleep, (3) substance abuse or significant medical conditions impacting sleep quality, and (4) inability to comply with study requirements (eg, wearing the smartwatch).

### Recruitment: Participant Recruitment and Screening

The recruitment methods are as follows: (1) physical (study invitations posted on university and public hospital bulletin boards), (2) digital (study invitations on professional networking platforms like LinkedIn), and (3) referral (snowball sampling through professional networks).

### Screening Process

The screening process begins with initial contact from interested participants. Structured remote interviews are then conducted to screen participants based on the inclusion and exclusion criteria. Only participants meeting all criteria proceed to an in-person meeting for informed consent and verification of eligibility documentation. Retention leverages the intrinsic motivation of participants for sleep improvement, along with structured touchpoints at the 3 assessments.

### Interventions

#### Control Intervention: Generic Sleep Hygiene Education

Control group participants receive standardized sleep hygiene education on day 30, covering general recommendations applicable to all adults. Examples include maintaining a consistent sleep-wake schedule and sleeping between 7 and 9 hours per night. These recommendations are not personalized to individual sleep patterns.

#### Experimental Intervention: Personalized ML-Derived Recommendations

Experimental group participants receive personalized behavioral recommendations from a predefined library (Multimedia Appendix 1) on day 30 based on individual ML model analysis of their baseline sleep data (days 1‐30).

### ML Framework for Personalized Interventions

Regarding data structure and variables, Samsung Galaxy Watch 4 generates 1 target variable (sleep_score) and 10 explanatory variables (sleep_duration, movement_awakening, sleep_cycle, mental_recovery, physical_recovery, efficiency, Transition_N1, Light_N2, Deep_N3, and REM) per sleep session. Through preprocessing, 5 additional features are engineered (real_total_sleep, Transition_pct, Light_pct, Deep_pct, and REM_pct), and temporal (Night_Number) and identifier (Participant_ID) variables are added, creating an 18-column dataset. For ML analysis, 15 variables are used as ML input variables (excluding sleep_score as the target, and Participant_ID and Night_Number as nonpredictive identifiers).

The ML framework serves as the mechanism for generating personalized interventions, not as the study outcome. We use established methods (eg, random forest and SHAP [Shapley Additive Explanations]) documented in ML literature to identify each participant’s top predictive sleep parameters. Our innovation is applying these tools to generate behavioral recommendations from consumer device data, not developing new algorithms.

### Model Architecture and Development

The 15 Samsung Galaxy Watch 4 explanatory variables and additional engineered features serve as the base dataset. The training-validation framework involves a temporal split using baseline period data (days 1‐30) with a 70/30 split for training/validation, cross-validation through 5-fold time-series cross-validation to prevent data leakage, and individual modeling for separate models trained for each participant. Models include random forest regression (primary model for interpretability), gradient boosting (extreme gradient boosting [XGBoost]) for comparison, and multiple linear regression as baseline, with selection based on cross-validation root mean square error and R². Feature importance and selection involve SHAP values for feature importance ranking, recursive feature elimination to identify the top 5 predictors per participant, and correlation analysis to avoid multicollinearity (threshold: *r*>0.8). Personalized recommendation generation is based on individual feature importance ranking, and participants receive targeted recommendations from a predefined library (Multimedia Appendix 1), with a focus on their top 2‐4 modifiable sleep parameters.

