### Pilot Objectives

The pilot objectives are as follows:

Feasibility: Can we successfully recruit, enroll, randomize, and retain participants? Can personalized ML interventions be delivered? Do participants engage with recommendations?Preliminary effect size estimation: What magnitude of difference between groups might we observe? What variability exists within groups? What baseline-to-follow-up correlation informs covariate adjustment? The estimates can inform future randomized controlled trial (RCT) sample size calculations.Methodology refinement: What challenges arise in data collection, ML model training, and intervention delivery? What proportion of nights yield usable data? Which sleep parameters show the most predictive value?Hypothesis generation: Does personalization show a promising signal warranting a larger trial? Do certain participant subgroups respond better?

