#### Exploratory Analyses: Hypothesis Generation Only

The exploratory analyses involve the following three aspects:

Individual parameter changes: Compare the change in specific sleep variables (duration, deep sleep percentage, and REM percentage) between groups using *t* tests (unadjusted for multiple comparisons, given the exploratory nature).Adherence subgroups: In the experimental group, compare outcomes between high (≥80%) and low (<80%) self-reported adherence using the Mann-Whitney *U* test.Predictive feature patterns: Perform a descriptive analysis of which sleep parameters are most frequently identified as the top predictors across participants.

All exploratory analyses are labeled hypothesis-generating, not confirmatory. No adjustments are made for multiple comparisons, given the pilot scope of the study. Regarding the handling of missing data for the primary outcome (sleep score), participants are excluded if sufficient night data are not available in the baseline and postintervention periods, and action on the secondary outcome (PSQI) is derived from the handling of the primary outcome. This protocol contains the complete statistical analysis plan, and no separate statistical analysis plan exists.

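### The tally of most frequent top predictors has no chance reference, and its chance level is both high and unequal across inputs

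*Protocol article*

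**What the plan says.** ML Framework for Personalized Interventions states that "15 variables are used as ML input variables". Model Architecture and Development fits a separate model for each person to "baseline period data (days 1‐30) with a 70/30 split for training/validation". It chooses among random forest (primary), XGBoost and linear regression, "with selection based on cross-validation root mean square error and R²". Feature selection combines SHAP ranking, "recursive feature elimination to identify the top 5 predictors per participant" and "correlation analysis to avoid multicollinearity (threshold: *r*>0.8". The section does not say whether the correlation screen comes before or after elimination, or which member of a correlated pair is kept. It requires no minimum performance before a person's predictors count.

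The third item of Exploratory Analyses: Hypothesis Generation Only reads: "Perform a descriptive analysis of which sleep parameters are most frequently identified as the top predictors across participants". It gives no list length and does not say whether 16 or 32 people contribute. It is the listed analysis that most directly answers the question in Pilot Objectives: "Which sleep parameters show the most predictive value". The same section states that no separate statistical analysis plan exists, so this wording is the full specification.

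**The concern.** Every participant must supply a list of fixed length, however poorly the model predicts. A count of such lists therefore always has a leader, and nothing in the plan shows how large a count chance alone would give. If the chance level also differs between inputs, the order of the counts reflects partly how each variable is recorded and duplicated, and only partly how well it predicts the score.

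What is at stake is the pilot's answer on which parameters carry predictive value. The Conclusions allow that consumer wearables may not yet support meaningful pattern detection in individuals. A tally without a null reference cannot show that outcome.

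**Working it through.** **Inputs from the article.** There are 10 device variables plus 5 engineered ones, so 15 inputs; adding 1 target and 2 identifiers gives the stated 18 columns. Elimination keeps 5. Each arm has 16 participants, 32 in total. Training nights are 30 × 0.70 = 21 at most, or 30 × 0.82 × 0.70 ≈ 17 after the expected 18% exclusion. The article states no chance level to reproduce.

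**Step 1: chance level.** If k names are drawn at random from P inputs, each input appears in k/P of lists, and in n·k/P of n lists. The leader's count was simulated (20,000 tallies per setting).

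| k of P | lists | chance per input | expected count | mean count of leader |
|---|---|---|---|---|
| 5 of 15 | 16 | 33.3% | 5.3 | 8.8 (5th-95th percentile 7-11) |
| 5 of 15 | 32 | 33.3% | 10.7 | 15.6 (14-18) |
| 4 of 15 | 16 | 26.7% | 4.3 | 7.6 |
| 2 of 15 | 16 | 13.3% | 2.1 | 4.8 |
| 5 of 10 | 16 | 50.0% | 8.0 | 11.2 |

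In the first row, the leader reaches 8 of 16 or more in about 93-94% of random tallies. Being named in half the participants is thus what noise gives the leader. The rows with 2 and 4 names are included because the article also speaks of the top 2-4 parameters. The last row shows the effect of a screen that runs first. In two simulations with assumed variable distributions, about 8.8 and 7.7 inputs survived such a screen, giving chance rates of 5/8.8 ≈ 57% and 5/7.7 ≈ 65%.

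**Step 2: unequal chance levels.** Recursive elimination to 5 with a random forest was run on 21 simulated nights. Inputs were built from the definitions in Tables 1 and 2, with assumed means and SDs, and the score was pure noise (150 runs, no screen).

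- sleep_cycle and efficiency: selected in 7% each.
- movement_awakening, physical_recovery and Transition_pct: 45-46%.
- With a screen at |r|>0.8 applied first and keeping the first-listed input (110 runs): from 0% to 75%.

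A forest's splits do not depend on units, so scale is not the cause. The sources are few distinct values (sleep_cycle is a small count, efficiency a rounded percentage), redundancy and screen order. Redundancy follows from the tables: efficiency = 100 × (sleep_duration − Transition_N1)/sleep_duration = 100 − Transition_pct, up to rounding. REM, REM_pct and mental_recovery all derive from the REM phase. Units matter only for the linear comparator: with unscaled inputs it picked sleep_cycle in 60% of noise runs, and after standardising in 3%.

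**Step 3: with real signal.** The score was given assumed dependence on sleep_duration, Deep_N3, REM and movement_awakening (90 runs, no screen).

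- sleep_duration was selected in 93% and its near-duplicate real_total_sleep in 91%, well above chance.
- Deep_N3 reached 51% and REM 44%.
- movement_awakening, a true driver, reached 41% against 46% under noise. The gap is within simulation error, so its count cannot be told from chance.

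Strong drivers stand out; weaker ones can be lost or misordered.

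**Step 4: what a correction must do.** Exceeding the shuffled mean is not enough. Group the inputs into seven families: REM/REM_pct/mental_recovery; Deep_N3/Deep_pct/physical_recovery; Transition_N1/Transition_pct/efficiency; Light_N2/Light_pct; sleep_duration/real_total_sleep; movement_awakening; sleep_cycle. With random lists of 5, a family of three appears with probability 1 − C(12,5)/C(15,5) = 1 − 792/3003 = 74%, a pair with 1 − 1287/3003 = 57%, a single with 33%. Under pure noise, about 3.5 of the 7 exceed their own mean, and at least one does in over 99.9% of tallies.

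Raw differences also mislead. In a simulation with two equal drivers, movement_awakening gained 3.8 and sleep_cycle 9.1 lists out of 16, because movement_awakening was already at 16 of 16 and had no room to rise.

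**The case against.** The strongest reply is that this is one descriptive item, and the article says so: "All exploratory analyses are labeled hypothesis-generating, not confirmatory". The article treats the ML framework as the means of generating advice and not as the study outcome, and no primary or secondary result depends on the tally. That stands, and it sets the weight of the point.

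Three stronger readings are tempting but not supported.

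- A reader might infer that the tally will be pure noise. The primary outcome section describes the score as a composite of duration, architecture, efficiency and fragmentation, which these inputs measure. Some signal is therefore expected, and Step 3 shows strong drivers rising above chance.
- A reader might take 33%, or the higher screened rates, as the tally's fixed chance level. The exploratory item does not tie the tally to five names, and the screened rates need an order and keep rule that the article does not state. The article also writes r>0.8, not |r|>0.8, so a negatively correlated pair such as efficiency and Transition_pct need not be screened.
- A reader might infer that this tally selects parameters for later trials. Implications for Future Research says only that the dataset will allow exploration of which parameters show reliable personalization effects.

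**Conclusion.** The point holds in limited form. The tally has no chance reference, and its chance level is substantial: 33% per input and a leader in about 8.8 of 16 lists for five names, or 13-27% and 4.8-7.6 of 16 for two to four. These figures need only random selection and the article's counts. That chance rates differ between inputs is well supported in direction, but the per-variable rates rest on assumed sleep distributions, which the article does not give. Noise can distort the ranking; it need not produce it alone. Severity is minor: an optional improvement to an exploratory analysis. It concerns the summary across participants, not the advice given to any one person.

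**What to change.** In Exploratory Analyses: Hypothesis Generation Only:

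1. State the list length, who is counted (experimental arm or all participants), and the order, sign and keep rule of the correlation screen.
2. Rerun the same selection pipeline on random reorderings of each participant's nightly sleep_score, for example 200 times. Report each parameter's or redundant family's observed frequency beside its shuffled distribution.
3. Name a leading predictor only if it exceeds an upper percentile of that null that allows for taking the largest. One choice is to standardise each excess by its shuffled mean and SD, and use the 95th percentile of the maximum across parameters or families.
4. Do not rank parameters by the raw difference between observed and shuffled frequency.

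The cost is a few sentences and some local computing: 16 × 200 = 3,200 pipeline runs, or 6,400 for all 32 participants. No new data are needed. The downside is that fewer parameters, possibly none, will be named.
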